#### Part II

2. The CBF parameter of oxy-Hb will significantly increase from time point 1 to time point 2 for all breakfast conditions.
This change will be significantly greater for the high-nitrate breakfast condition compared with the low-nitrate and no breakfast conditions.3. Deoxy-Hb will decrease for all conditions from time point 1 to time point 2.
The decrease will be significantly greater for the high-nitrate breakfast compared with the low-nitrate and the no breakfast conditions.4. Arterial stiffness will significantly decrease after the high-nitrate breakfast condition.
The decrease will be significantly greater in the high-nitrate breakfast compared with the low-nitrate and no breakfast conditions.5. Psychological factors (i.e. mood, alertness, and less sleepiness) will improve from time point 1 to time point 2 for the high-nitrate condition
The improvement in psychological factors will be significantly greater for the high-nitrate breakfast compared with the low-nitrate and no breakfast conditions.6. Working memory performance will significantly improve in the low-nitrate breakfast condition from time point 1 to time point 2.
This improvement will be significantly different from the no breakfast condition.7. Oxy-Hb will increase from time point 1 to time point 2 for the low-nitrate breakfast condition.
This increase will be significantly greater for the low-nitrate breakfast compared with the no breakfast condition.8. Deoxy-Hb will significantly decrease for the low-nitrate breakfast condition.
This decrease will be significantly different from the no breakfast condition.9. Arterial stiffness will significantly decrease in the low-nitrate breakfast condition.
This decrease will be significantly different from the no breakfast condition.10. Psychological factors (i.e. mood, alertness, and less sleepiness) will improve from time point 1 to time point 2 for the low-nitrate breakfast condition
This difference will be significantly greater for the low-nitrate breakfast condition compared with the no breakfast condition.11. Salivary nitrate/nitrite levels will be significantly higher after the high-nitrate breakfast at time point 1 and time point 2 compared to the low-nitrate and no breakfast conditions, and higher for low-nitrate vs. no breakfast.

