### Hypotheses

#### Part I

Working memory performance will significantly improve from immediately after the breakfast (time point 1) to 130 min after the breakfast (time point 2) in the high-nitrate breakfast condition.
This improvement will significantly differ from the low-nitrate or the no breakfast conditions, where there will be no change or a reduction in working memory performance.

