**Fig 2 pone.0285581.g002:**
[figure not shown]
Timeline of measurements and experimental conditions. WM = working memory; fNIRS = functional near-infrared spectroscopy.

On the first breakfast test-day (either condition B or C), participants will be able to choose how much food they want to consume from the foods provided. Foods will include: wholemeal bread, cheese, ham, cucumber, yoghurt, and muesli with low sugar content. On subsequent visits the same and exact amount of food (breakfast will be weighed and documented) will be given to the participants. The breakfast consumption should be as close to the participant’s habitual diet as possible, hence why participants can choose the amount of breakfast that they deem will satisfy them. The breakfast provided will be the same in both breakfast conditions and will not contain foods that have a high glycaemic index (e.g. white bread), to reduce the effects of glucose. Previous research has indicated that postprandial blood glucose concentrations could mediate the effects of breakfast on cognitive function [33]. However, a small amount of orange juice will be provided in both breakfast conditions; primarily to help wash down the taste of the concentrated beetroot juice in the high-nitrate breakfast condition. Participants are allowed to drink water ad libitum throughout the course of each experimental day; however, amounts of fluid will be attempted to be matched for each experimental condition. The amount of nitrate provided in the high-nitrate breakfast condition will be adjusted for weight of the participant and they will be asked to drink all the concentrated beetroot juice. Each 60 ml concentrated beetroot juice shot (product of Umara AB, Sweden) contains 500 mg of nitrate. The amount of nitrate provided will be based on the daily acceptable limit of 3.7 mg per kg body weight per day [50], so for a 40 kg individual the amount of nitrate would be 148 mg. In the scenario that the participant does not consume all the beetroot juice, then the amount they consumed will be documented. There should be very little variation in nitrate content between the shots as they are designed to contain 500 mg of nitrate per 60 ml of concentrated beetroot juice and are all taken from the same batch.

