#### Saliva nitrate/nitrite concentrations

Nitrate and nitrite concentrations will be collected via three saliva samples: one before the experimental conditions (time point 0) and at two time points (time points 1 and 2) after the experimental conditions (**Fig 2**). Cotton buds in test tubes will be used to collect the saliva. These samples will be centrifuged and stored at -80°C, until the time of analysis (<6 months from collection). The OxiSelect™ In Vitro Nitric Oxide (Nitrite/Nitrate) Assay Kit (Fluorometric) from Cell Biolabs, Inc. (San Diego, CA, USA) will be used to measure nitrate (NO_3_^-^) and nitrite (NO_2_^-^) levels collected from the saliva samples.

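### Juice left in the mouth can distort the time point 1 saliva comparison and the modelled change from time point 1 to time point 2; the exposure check should run from time point 0 to time point 2

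*Protocol article*

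**What the plan says.** **Timing.** Hypotheses, Part I, sets the two occasions after breakfast as "immediately after the breakfast (time point 1) to 130 min after the breakfast (time point 2". The section on saliva nitrate/nitrite concentrations plans three samples per visit, "one before the experimental conditions (time point 0) and at two time points (time points 1 and 2) after the experimental conditions", and describes collection in one line: "Cotton buds in test tubes will be used to collect the saliva".

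**Drink.** Experimental conditions gives the beetroot juice in the high-nitrate condition only. The shots are "designed to contain 500 mg of nitrate per 60 ml of concentrated beetroot juice". A small orange juice accompanies both breakfasts, and water is freely available in every condition.

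**Hypothesis.** Hypothesis 11 (Hypotheses, Part II) has a high-nitrate part, "Salivary nitrate/nitrite levels will be significantly higher after the high-nitrate breakfast at time point 1 and time point 2", compared with both other conditions. It adds a second part: "and higher for low-nitrate vs. no breakfast".

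**Analysis.** The first subsection of Statistical methods applies linear mixed models to the change in nitrate/nitrite between time points 1 and 2. Further models with condition and time interactions then compare those changes across conditions. Time point 0 has no stated role in the saliva analysis.

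**The concern.** Time point 1 is a post-drink sample, yet the model uses it as the starting value. A cotton bud placed in a mouth that has just held concentrated nitrate juice can pick up that juice as well as saliva. The Introduction notes that nitrate is converted to nitrite in the mouth, so residue could affect both analytes.

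There are two consequences. First, a high-nitrate difference at time point 1 would be weak evidence that nitrate had been absorbed and returned to saliva. The article's own timing rationale puts the plasma nitrite peak in adults at 2.5 to 3 hours after ingestion, so a sample this early is poorly placed to show uptake. Second, the modelled change would be biased downwards in the one condition where a rise is of interest.

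Salivary nitrate/nitrite is a named secondary outcome and the only listed biological measure of nitrate exposure. If working memory shows no effect, this measure helps to tell whether nitrate had no effect or whether exposure was not raised.

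**Working it through.** **1. The plan's own figure.** Experimental conditions states 148 mg nitrate for a 40 kg participant at 3.7 mg/kg. Check: 3.7 × 40 = 148 mg, which agrees.

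**2. Juice concentration.** Inputs: 500 mg per 60 ml (Experimental conditions), and the molar mass of nitrate, 62.0 g/mol (a chemical constant, not in the article).

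- 500 / 60 = 8.33 mg/ml = 8.33 g/L
- 8.33 / 62.0 = 0.134 mol/L, or about 134 mmol/L
- Volume drunk at 40 kg: 148 / 8.33 = 17.8 ml

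**3. Effect of residue on a reading.** Added concentration = 134 mmol/L × fraction of the sampled fluid that is juice. The fractions are assumed, because the article gives no clearance rate.

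| Assumed juice fraction | Added nitrate (mmol/L) |
|---|---|
| 0.1% | 0.13 |
| 1% | 1.3 |
| 5% | 6.7 |

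Put the other way, bringing residue below 1 mmol/L needs about 134-fold dilution (134 / 1), and below 0.1 mmol/L about 1,340-fold (134 / 0.1). The article gives no background salivary level for comparison.

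**4. Where the residue enters the contrasts.** Let H and L be the high-nitrate and low-nitrate conditions, with true mean levels H0, H1, H2 and L0, L1, L2 at time points 0, 1 and 2. Let r be the residue at time point 1 in H, taken as negligible at time point 2. L contains no beetroot juice.

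- Level difference at time point 1: (H1 − L1) + r, inflated by r.
- Change in H from time point 1 to 2, as planned: (H2 − H1) − r, deflated by r and negative once r exceeds H2 − H1.
- Condition-by-time contrast, as planned: [(H2 − H1) − (L2 − L1)] − r, deflated by r.
- Difference in change from time point 0 to 2: (H2 − H0) − (L2 − L0), free of r.

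The same holds with no breakfast in place of L. The low-nitrate versus no-breakfast comparison contains no r at all.

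**5. Timing that can be read from the text.** Of the 130 min from breakfast to the last measurement, 80 min are the sitting period, leaving 130 − 80 = 50 min for everything else. The place of the saliva sample within time point 1 is in Fig 2, which is not available here. A later slot would mean a smaller r.

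**The case against.** A reader might infer that residue alone could confirm the whole of Hypothesis 11 without any uptake. The documents do not support that. The hypothesis also requires a difference at time point 2, about 130 min after breakfast, and a difference between two conditions that contain no beetroot juice. Residue from drinking explains neither. Hypothesis 11 is also worded as salivary level and makes no claim about absorption, so the weakness lies in using time point 1 as evidence of exposure.

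A reader might also infer that samples are taken with no oral clearing. The article describes no rinse or wait, but it is a condensed account, and such bench detail commonly sits in the full procedure. The ban on chewing gum and antibacterial mouthwash shows that oral conditions were considered. Orange juice and water would clear some residue, although neither is described as a fixed rinse tied to sampling. The missing rinse is therefore not counted as an error.

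Three further objections carry weight. The residue fractions are assumed and span 50-fold, so materiality is possible but not shown. Saliva is not the only exposure information, since the juice comes from one batch of known content and incomplete intake is recorded. The interaction model could also yield a condition contrast at time point 2 that is free of residue, and Hypothesis 11 does not itself predict a rise between time points 1 and 2.

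What remains is that the analysis the article states for saliva is the change from time point 1 to time point 2. That contrast carries the residue in full and leaves out the pre-breakfast sample.

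**Conclusion.** The point holds for two elements: the time point 1 part of Hypothesis 11, and the salivary change from time point 1 to time point 2 in Statistical methods. Residue would inflate the first and deflate the second by the same amount, in the high-nitrate condition only. An assumed residue of 0.1% to 5% gives about 0.13 to 6.7 mmol/L. The true size cannot be computed, because the residue, the background level and the sampling minute are not given.

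The conclusion assumes that the time point 1 sample follows the juice closely enough for some to remain, as the definition of that time point implies, and that little remains by time point 2. It does not extend to time point 2 levels, to low-nitrate versus no breakfast, or to the primary working-memory analysis.

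**What to change.** **Analysis (the main change).** In the saliva part of Statistical methods, include time point 0 in the mixed model. Rest the exposure conclusion on the between-condition difference in change from time point 0 to time point 2. Report time point 1 separately, stating that high-nitrate values may include juice left in the mouth. This needs a few sentences and no new samples, since time point 0 saliva is already collected at every visit. It should be fixed before the saliva results are examined.

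**Procedure (optional).** If the full procedure already has an oral clearing step or a delay before the time point 1 sample, state it. If not, one may be added only for participants who have not yet started, so that handling is the same across each participant's three conditions. Trial status reports that data collection began in late February 2022, so a change partway through a participant's visits would mix handling with condition in a crossover. The cost is an assumed one to two minutes per sample, plus a flag marking which participants were sampled under which procedure. The analytic change stands without it.

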## Methods

### Study design

This study is a randomised crossover trial with three experimental conditions. The experimental procedures will occur at the Swedish School of Sport and Health Sciences (GIH) in Stockholm, Sweden. The researchers will visit the schools of potential participants to carry out familiarisation visits. Alternatively, the potential participants will visit GIH, if deemed more convenient for the participants. A schedule of enrolment, interventions, and assessments can be found in **Fig 1**.

**Fig 1 pone.0285581.g001:**
[figure not shown]
Schedule of enrolment, interventions, and assessments for a 3-arm, randomised, crossover study design.

After completing the familiarisation, the participants will participate in three experimental days consisting of three randomly ordered experimental conditions. A minimum washout period of six days will be in place to reduce any carry-over effects from the previous condition [44, 45]. Most often the participants will come in on the same weekday, three weeks in a row. Two participants will be tested on the same test day, with a 20-minute gap in starting times. There will be a 24 hour monitoring and standardisation of physical activity, sleep, and dietary intake for all participants one day before each test-day. Participants will receive a 500 SEK (~€47) gift card for their participation.

#### Ethical approval and consent to participate

This study obtained ethical approval from the Swedish Ethical Review Authority, Stockholm, Sweden (Dnr: 2021-07053-01). The trial registration can be found at: https://doi.org/10.1186/ISRCTN16596056. Written informed consent will be obtained by the participants and guardians before data collection begins. Compensation will be provided to any participant in case they are harmed due to the study. This study is part of larger project called “Physical activity for healthy brain functions in school youth”. The results from this project will be directly used in the planning of interventions that will be implemented in schools in the Stockholm area.

### Participants

Schools will be selected from the Stockholm region. Both the participants and guardian/s must sign and provide consent before data collection begins. Inclusion criteria for participants are adolescents in grades 7–9 (approximately from ages 13 to 15 years), attending schools in the Stockholm area, and can understand Swedish. Those that have been diagnosed with diabetes, epilepsy, vascular health conditions/circulatory abnormalities, or have visual/auditory impairments will be excluded. Participants will be informed that they can decide to drop out at any time without explanation.

### Familiarisation visit

The researchers will visit the schools prior to randomisation in order to introduce all the procedures that will be carried out on the test days to the participants and perform any initial measurements. This will include practising the cognitive tests (as to reduce practice effects), showing the fNIRS cap, describing how arterial stiffness is measured, and being familiarised with the questionnaires for measuring psychological factors. Demographic and other data for important measures will also be collected, these will include: age, sex, head measurements (i.e. circumference, nasion to inion, and between pre-auricular points for fNIRS cap size and head registration in the analysis), food allergies or any dietary intolerances, and a health declaration questionnaire.

Additionally, a short questionnaire will be provided for the participants, asking them how often they consume various nitrate-rich foods (pictures of foods will be provided) and how often they eat breakfast. This is to assess the proportion of regular consumers of nitrate-rich foods and the proportion of those that habitually consume breakfast. Schedules for organised sport and physical education classes will also be collected in order to standardise physical activity on pre-test days and to organise consistent times for participants to visit the lab for the data collection.

Post-familiarisation, participants will be paired according to head size (for practicality in fNIRS measuring of two participants on the same day) randomised by the researchers via a computer-generated random order of experimental conditions that is equally assigned to every participant. The randomisation will be password-protected and will not be assigned to the participants until the recruitment and familiarisation stages are finished.

### Pre-experimental monitoring

To standardise experiments, participants will be asked to keep their physical activity levels on pre-test days consistent, and to record details about their physical activity, diet, and sleep in a standardised diary. They will also be asked to wear accelerometers that monitor their physical activity and sedentary time during the day (hip-worn Actigraph GT3X+ or wGT3X-BT) and sleep at night (wrist-worn Actigraph GT3X+ or wGT3X-BT). Variables from Actigraph will include total time spent in physical activity and percentages of time in sedentary, light, and moderate-to-vigorous physical activity, according to the standardised Evenson cut-points [46]. Throughout the night on pre-test nights, participants will wear the Actigraph GT3X+ on their left wrist [47]. An algorithm for sleep-wake scoring in children will be used [48], and variables of sleep analysed will include: time to sleep onset, sleep efficiency, times waking up after sleep onset, and total sleep. The diaries will provide complementary information regarding times of waking up, going to bed, and sleep quality. Measured physical activity, sedentary time, and sleep parameters will be used to confirm compliance to the study protocol and for adjustment in statistical analyses.

Within the diary, dietary information will be recorded by the participants to standardise dietary intake on pre-test days. A diet and nutrition analysis software (Dietist Net Pro, http://www.kostdata.se/se/dietist-net/dietist-net-pro) will be used to analyse the nutrient intake of pre-test day meals of the participants. Participants will be asked to avoid foods that are rich in nitrate on pre-test days and fast after dinner until they come to GIH on test mornings. Additionally, participants will be asked to not consume chewing gum or use anti-bacterial mouthwash on test days as these can inhibit oral nitrate metabolism [4, 49]. One of the researchers will send a text message to the participants two days before the test days to remind them about the standardisations mentioned.

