## Introduction

Inorganic nitrate can be obtained from diet, through sources such as rocket (rucola), spinach, lettuce, and beetroot [1], with green leafy vegetables contributing to the majority of nitrate consumption [2]. Dietary nitrate is converted into nitrite in the oral cavity, with some of the consumed nitrite being reduced in the stomach to nitric oxide (NO) [3]. However, nitrite is also absorbed into the bloodstream and distributed across the tissues in the body. There, nitrite can be reduced to bioactive NO by several different processes [4]. NO is an important molecule involved in many systemic and cerebral physiological processes. Previous studies have demonstrated its beneficial effects on blood pressure [5–9], endothelial function [8, 9], arterial stiffness [3, 7, 10], and mitochondrial respiratory efficiency in human skeletal muscle [11], whereas inadequate NO has been associated with greater risk for cognitive decline [12, 13]. Despite this knowledge, randomised controlled trials (RCTs) examining the effects of dietary nitrate on cognitive function have been few, with small sample sizes, and only in adult populations, resulting in mixed results [14]. Therefore, more studies of higher quality and in other populations that could benefit from the effects of nitrate, such as adolescents, are needed.

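### The chewing-gum and anti-bacterial mouthwash ban covers only the test day, so mouthwash the evening before a morning nitrate dose is allowed and may weaken the high- versus low-nitrate contrast

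*Protocol article*

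**What the plan says.** The Introduction of the Protocol article states the mechanism on which the intervention depends: "Dietary nitrate is converted into nitrite in the oral cavity". Pre-experimental monitoring then protects that step with one instruction: "participants will be asked to not consume chewing gum or use anti-bacterial mouthwash on test days as these can inhibit oral nitrate metabolism".

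The sentence just before it uses an earlier window: "Participants will be asked to avoid foods that are rich in nitrate on pre-test days and fast after dinner", with the fast lasting until arrival on the test morning. Study design sets the same window more generally: "There will be a 24 hour monitoring and standardisation of physical activity, sleep, and dietary intake for all participants one day before each test-day". A text message two days before each test day reminds participants of these rules.

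The diary is described as recording physical activity, diet and sleep. Mouthwash and gum are not among the listed items. Saliva for nitrate and nitrite is taken before each condition and at two time points after it, then frozen and assayed within six months of collection (Saliva nitrate/nitrite concentrations).

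**The concern.** The protocol names these products as able to inhibit the conversion it relies on, yet its ban begins only on the day of dosing. Breakfast and the beetroot juice are given in the morning after an overnight fast. The part of the ban that precedes the dose is therefore short, and a participant who uses anti-bacterial mouthwash at bedtime has followed every instruction.

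If inhibition lasts overnight, such a participant receives the nitrate but forms less nitrite from it. The loss falls mainly on the high-nitrate visit, where the nitrate is given. Comparing participants with themselves does not cancel it. It would attenuate the primary high- versus low-nitrate contrast on working memory and the nitrite part of Hypothesis 11, and would make a null result somewhat harder to interpret.

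**Working it through.** **Windows side by side**

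| Rule | Pre-test day | Test day |
|---|---|---|
| Avoid nitrate-rich foods | yes | not stated separately; fasted on arrival, breakfast supplied |
| Standardise activity, sleep, diet | yes | not applicable |
| No gum or anti-bacterial mouthwash | **no** | yes |

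The only rule aimed at conversion is the one that does not reach the evening before the dose.

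**Inputs for size** (Sample size section): effect of nitrate on working memory d = 0.63, giving n = 22; two-sided α = 0.05; 0.8, printed as β and read here as power; largest component n = 36; seven added, total 43. The share f of high-nitrate visits with no nitrate effect is not in the documents. It is an assumption, run from 0 to 40%.

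**Reproducing the plan.** For a paired t-test, power = P(|T| > t₀.₉₇₅,ₙ₋₁), where T is noncentral t with n − 1 degrees of freedom and noncentrality d√n. At d = 0.63, n = 22 gives power 80.4%, so the stated 22 is reproduced.

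**Dilution.** If a share f has zero effect and the rest have 0.63 (in units of the SD of the paired difference):

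- mean effect = 0.63(1 − f)
- the mixture adds variance 0.63² f(1 − f), so d_eff = 0.63(1 − f) / √(1 + 0.63² f(1 − f))
- example, f = 0.20: 0.504 / √(1 + 0.3969 × 0.16) = 0.504 / 1.031 = 0.489

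| f (assumed) | Mean effect | d_eff | n for 80% power | Power, 36 completers | Power, 34 completers |
|---|---|---|---|---|---|
| 0 | 0.630 | 0.630 | 22 | 95.7% | 94.6% |
| 5% | 0.598 | 0.593 | 25 | 93.3% | 91.9% |
| 10% | 0.567 | 0.557 | 28 | 90.1% | 88.4% |
| 20% | 0.504 | 0.489 | 35 | 81.4% | 79.0% |
| 30% | 0.441 | 0.424 | 46 | 69.6% | 66.9% |
| 40% | 0.378 | 0.361 | 63 | 55.9% | 53.4% |

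The 36 column follows the plan (43 − 7 = 36). The 34 column is what remains if a full 20% of 43 leave (43 × 0.8 = 34.4). With 36 completers, power reaches 80% for f up to 21.2%. Ignoring the added variance, the required n at f = 5%, 10% and 20% is 24, 27 and 33, which is close to the table.

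The margin exists because the trial is sized on the smaller breakfast effect on psychological factors (0.48), not on the nitrate effect. The margin protects power only: at any f above zero the estimated mean effect is still reduced by the factor 1 − f.

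**The case against.** The strongest case against has five parts.

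1. **Different purposes.** The diet rule standardises intake and the mouthwash rule protects metabolism, so different windows are not a contradiction. The test-day ban also covers the 130 minutes after breakfast, when conversion happens. This stands. The point is that the rule is narrow for its own stated purpose, not that two passages conflict.

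2. **No duration of inhibition is given.** A reader might infer that evening users cannot convert the dose and that the effect is diluted. The documents support only that conversion may be reduced. They give even less reason to expect overnight carry-over from gum, which is included in the fix only because it shares the sentence.

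3. **Antibiotics.** The exclusion list ("Those that have been diagnosed with diabetes, epilepsy, vascular health conditions/circulatory abnormalities, or have visual/auditory impairments will be excluded") does not mention them, and a reader might infer that antibiotic use goes unscreened. That does not follow. The Familiarisation visit section collects "food allergies or any dietary intolerances, and a health declaration questionnaire", whose content is not shown and which may already ask.

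4. **The saliva samples.** These could show poor conversion, so it is too strong to say that a null result would be uninterpretable. They detect the problem only after the visit, however, and cannot prevent it.

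5. **Power and the one-condition model.** The planned power survives any modest f. A habitual evening user would be affected on all three visits, and Hypothesis 11 expects a nitrate/nitrite difference even between low-nitrate and no breakfast. Loss confined to the high-nitrate visit is therefore a simplification.

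**Conclusion.** The concern holds in limited form. The instruction leaves the evening before a morning dose uncovered, although the protocol already has a pre-test-day window into which it would fit. Any resulting bias would be towards no difference in the high- versus low-nitrate contrast and in the nitrite part of Hypothesis 11.

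Its size cannot be determined from the documents. The calculation assumes complete loss of effect in a share f of high-nitrate visits and the plan's own d = 0.63, which comes from adults. On that basis, planned power is kept with 36 completers unless f exceeds about 21%. With 34 completers it is just under 80% at f = 20%. A reader might conclude that the trial is underpowered or invalid for this reason, and nothing in the documents supports that. This is an inexpensive tightening of a stated rule.

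**What to change.** Extend the anti-bacterial mouthwash and chewing-gum instruction to pre-test days as well as test days, matching the nitrate-food rule. The reminder sent two days ahead already refers to these rules and arrives in time, so only the window it states needs to change. Record compliance with a line in the existing diary or one question on arrival. That question could also ask about antibiotics if the health declaration does not.

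The cost is a few words in the instruction, one recorded item per visit and a slightly longer restriction for participants. No stated sample size changes. The Trial status section says data collection began in late February 2022, so the change can help only visits still to come.
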